### Measurements

#### Overview

Table 1 gives an overview of all measurements. Participants are asked to fill out the questionnaires at baseline (T0); 3 months after the baseline measurement (T1); and 6 months after the baseline measurement (T2).

**Table 1 Tab1:** Overview of study parameters, measurement instruments and measurement points

Measure	Instrument	Filled out by Person with dementia	Informal caregiver
*Inclusion criterion*			
*(Very) Mild dementia*	CDR	T0	T0
*Exclusion criterion*			
*Trauma*	MINI Psychiatric Interview, module PTSD	T0	
*Primary outcome measure*			
*Neuropsychiatric symptoms of person with dementia*	NPI, total score		T0, T1, T2
*Secondary outcome measures*			
*Caregiver burden*	NPI, module Distress		T0, T1, T2
	EDIZ		T0, T1, T2
	TOPICS-MDS, modules Time investment and Burden		T0, T1, T2
*Quality of life of caregiver*	TOPICS-MDS, modules CarerQol and Quality of life (RAND-36 and variant of Cantril’s Self Anchoring Ladder)		T0, T1, T2
*Health of caregiver*	TOPICS-MDS, module Health (RAND-36)		T0, T1, T2
*Health-economic evaluation*			
*Care consumption*	TOPICS-MDS, module Use of care		T0, T1, T2
*Health-related quality of life of person with dementia*	TOPICS-MDS, module EQ5D + Cognitive	T0, T1, T2	
*Personal Information*			
*Socio-demographics*	TOPICS-MDS, module General data		T0
*Personal functioning of person with dementia*	TOPICS-MDS, modules Daily functioning (Katz-15) and Social functioning (RAND-36)	Daily functioning: T0, T1, T2	Daily functioning & Social functioning: T0, T1, T2
*Health of person with dementia*	TOPICS-MDS, modules Health and Multimorbidity	Health: T0, T1, T2	Multimorbidity: T0, T1, T2
*Psychological well-being of person with dementia*	TOPICS-MDS, module Psychological well-being	T0, T1, T2	
*Quality of life of person with dementia*	TOPICS-MDS, module Quality of life (RAND-36 and variant of Cantril’s Self Anchoring Ladder)	T0, T1, T2	
*Longer term outcome*			
*Nursing home admittance*	Addressed in month 18 with general practitioner		
*Process evaluation*			
*Other (reminiscence) activities*	Open question		T1, T2
*Use of OLSB*	Open questions		T1, T2

#### Primary outcome

##### Neuropsychiatric symptoms (NPS)

To assess the effect of the intervention on the primary outcome, neuropsychiatric symptoms, the Neuropsychiatric Inventory (NPI) will be used at all three time points in all participants. The NPI is a reliable and valid measure that is filled out by the primary informal caregiver [41]. The NPI is often used to measure neuropsychiatric symptoms, also in pharmacological and psychosocial intervention studies. The instrument is developed by Cummings (1994) and translated in Dutch by De Jonghe, Borkend and Kat (1997) [42]. The NPI measures the frequency, severity and distress of twelve neuropsychiatric symptoms (Delusions, Hallucinations, Agitation/Aggression, Depression/Dysphoria, Anxiety, Elation/Euphoria, Apathy/Indifference, Disinhibition, Irritability/Lability, Aberrant motor behavior, Sleep and Nighttime Behavior Disorders, and Appetite and Eating Disorders). The frequency (F) is provided on a scale from 0 = never to 4 = daily, the severity (S) on a scale from 0 = not to 3 = severe. The score for each of the twelve symptoms is computed as the frequency multiplied by the severity, resulting in a score ranging from 0 to 12. An FxE score of 4 or higher is seen as clinically relevant symptoms. The twelve FxE scores are added to a total score (0-144) or to four scores of symptom clusters: hyperactivity, psychosis, affective symptoms, and apathy [43].

#### Secondary outcomes

The majority of the secondary outcomes and the personal information is assessed with parts of The Older Persons and Informal Caregivers Survey Minimum DataSet (TOPICS-MDS) [44]. The TOPICS-MDS was developed to examine the effects of the initiatives that are part of the Dutch National Care for the Elderly Programme.

##### Caregiver Burden

Caregiver burden is a secondary outcome measure. It is measured with a Dutch questionnaire (Ervaren Druk door Informele Zorg or EDIZ) [45]. This instrument has been used in informal caregivers with dementia and proved to be reliable and valid in this group. The informal caregiver rates the subjective burden on nine items with a five-point scale ranging from 1 = no! to 5 = yes!. The answers are dichotomized per item and then added up to a score between 0 and 9.

Caregiver burden is also measured with the distress scales of the NPI [41, 42]. The caregiver rates the distress for each of the twelve neuropsychiatric symptoms on a scale from 0 = none to 5 = severe. These twelve distress scores are summarized to a total score, ranging from 0 to 60. This sum score provides an indication of the emotional distress caused by all neuropsychiatric symptoms. Thirdly, the modules Time investment and Burden of the TOPICS-MDS are used to assess caregiver burden.

##### Quality of life of the caregiver

The care-related quality of life of the caregiver is measured with the CarerQol [46]. This reliable and valid instrument asks seven questions that are rated on a three-point scale (0 = none to 3 = many). Caregivers also answer a general question on happiness on a visual analogue scale ranging from 0 to 10. The total score provides an indication of the care related quality of life of the informal caregiver. The CarerQol is part of the TOPICS-MDS. In addition, the general quality of life of the caregiver is assessed with the module Quality of life of the TOPICS-MDS. The latter module consists of questions of the RAND-36 [47] and a variant of Cantril’s Self Anchoring Ladder [48] in which persons are asked to rate their life on a scale from 1 to 10.

##### Health of caregiver

The general health condition of the caregiver is measured with the module Health of the TOPICS-MDS. This consists of two questions of the RAND-36 [47].

#### Health-economic evaluation

*Care consumption* of the person with dementia will be used in the preliminary health-economic evaluation that provides a time window of 6 months, parallel to the RCT. Care consumption is measured in the TOPICS-MDS [44]. Care consumption includes medical costs (e.g., visits of general practitioner, specialist physicians, and hospital care) as well as indirect non-medical costs (e.g., home care, travel costs). Costs will be evaluated, based on the manual of Tan et al. (2012) [49].

##### Health-related quality of life of person with dementia

To measure health-related quality of life, the EQ5D + Cognitive will be used [50], a short questionnaire with 6 items that is also part of the TOPICS-MDS. This study will use Dutch tariffs to calculate the quality adjusted life years (QALYs) to obtain a utility score.

#### Personal information

##### Socio-demographics

The following socio-demographics of both the persons with dementia as well as their caregivers are assessed: sex, age, education, marital status and cultural background. These questions are part of the TOPICS-MDS, module General Data [44]. Additionally, the name of their general practitioner is also asked, so they can be informed about the participation in the study.

##### Personal functioning of person with dementia

Personal functioning is measured with the modules Daily functioning and Social functioning of the TOPICS-MDS. This module consists of the Katz-15-ADL [51] and a question of the RAND-36 [47].

##### Health of person with dementia

The general health condition and the multimorbidity are assessed with the modules Health and Multimorbidity of the TOPICS-MDS. The latter consists of a list of 17 common diseases.

##### Psychological well-being of person with dementia

The psychological well-being is measured with the module Psychological well-being of the TOPICS-MDS. This module consists of questions (5) of the RAND-36 [47].

##### Quality of life of person with dementia

The module Quality of life of the TOPICS-MDS is being used to measure the quality of life of the person with dementia. This module consists of two questions of the RAND-36 (2) about quality of life in general and at this moment [47] and a variant of Cantril’s Self Anchoring Ladder [48] in which persons are asked to rate their life on a scale from 1 to 10.

#### Longer term outcome

##### Nursing home admittance

The longer term outcome is (time to) admittance to a nursing home. This will be assessed for all participants in month 18 of the study together with the general practitioner.

#### Process evaluation

The intervention will be evaluated in two ways: a content analysis of Online Story Books and through qualitative interviews. Participants will be asked for renewed informed consent for this part of the study, after they constructed the Online Life Story Book, as they can only then judge whether or not they want to share it with the research team. A content analysis of twenty randomly chosen Online Life Story Books will be carried out.

Qualitative interviews will be conducted using an existing narrative method [52] after the study has been completed. Stakeholders (professionals (care manager, psychologist, coordinator of volunteer work, social worker), volunteers, participants and their informal caregivers) will be asked to provide stories about specific moments before, during, and after the intervention. Each interview will last about 1 h.

Next to the content analysis and interviews, at T1 and T2 participants are asked questions regarding:

##### Reminiscence Activities

In order to ascertain whether persons in the control group did not create an online life story book or have undertaken similar activities during the study, the informal caregivers are asked a question about which reminiscence activities the person with dementia has undertaken.

##### The use of the Online Life Story Book

Participants are asked how often and how long the book in general and the online version of the book is used.

### Statistical analyses

#### Descriptive statistics

First, a CONSORT flow diagram will be made that shows the flow of the participants as well as the number of participants and the reasons for dropping out of the intervention or the study. Descriptive analyses will provide insights in the major characteristics of the persons with early dementia and the informal caregivers that participated in the study. These include personal information and functioning (TOPICS-MDS), neuropsychological complaints (NPI), caregiver burden (NPI and EDIZ) as well as quality of life of the person with dementia (EQ5D + Cognitive) and the caregiver (CarerQOL). Comparison with existing data of the TOPICS-MDS will give more information about the group that was actually reached.

#### Randomization check

Chi-square tests and t-tests will be used to check whether the randomization has succeeded in terms of personal information and functioning (TOPICS-MDS), neuropsychological complaints (NPI), caregiver burden (NPI and EDIZ), quality of life of the person with dementia (EQ5D + Cognitive), and quality of life of the caregiver (CarerQOL). When significant differences are found at baseline, we will assess whether these attenuate the outcomes later in time. If that is the case, we will control for these confounding variables in later analyses on the effects of the intervention.

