#### Sample size calculation

Based on systematic reviews [15, 17, 18], a small significant effect is expected for the primary outcome at follow-up. Hence, 74 participants are needed (GPower: f = 0.15; alpha = .05; power = .80; repeated measures anova with 2 groups and 3 measurement points; *r* = .50 between measurements). Given the vulnerability of the participants and a high mortality rate, we expect a drop-out of 30% [15, 17, 18]. Hence, 106 participants need to be included, 53 per condition.

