### Randomization

After the participant is included in the study, signed the informed consent, and participated in the baseline measurement, randomization will be carried out. Randomization will be done by an independent researcher at the University of Twente, based on a computer-generated list of random numbers.

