#### Effects

To analyze the effects on the primary outcome (total neuropsychiatric symptoms), repeated measures MANOVA will be used to assess the group differences across time. The condition (intervention vs. control) is the independent variable and the outcome measures across the three measurements are the repeated dependent variables. Simple contrasts will be used post-hoc to compare the post-intervention and follow-up measures with the pre-intervention measures. Effect sizes at post-intervention and follow-up will be calculated as Cohen’s d. Effect sizes between .56 and 1.2 are interpreted as large, between .33 and .55 as moderate, and below .33 as small [53].

We will also tentatively study the effects of the intervention on the four clusters of neuropsychiatric symptoms (hyperactivity, psychosis, affective symptoms, and apathy). As these measures are often not normally distributed, we will use a dichotomized outcome (clinically relevant symptoms or not, based on a FxS score of 4 and higher) [43]. We will carry out four logistic regression analyses with condition (intervention versus control) and presence of clinically relevant symptoms within the respective clusters at baseline as independent variables and presence of clinically relevant symptoms at follow-up as dependent variable. The odds-ratios will be used to provide estimates of the effect sizes in terms of Cohen’s d.

For the secondary outcome measures, three repeated measures MANOVA’s will be conducted, similar to the analysis for the primary outcome. The effect sizes will be given in Cohen’s d.

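### Baseline significance tests, followed by an outcome check with no criterion, choose the covariates: the primary model's covariate set is not fixed in advance, and predictors without significant imbalance stay out

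*Protocol article*

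**What the plan says.** Under Randomization, an independent researcher allocates participants after the baseline measurement, "based on a computer-generated list of random numbers". No stratification is mentioned.

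Under Randomization check, "Chi-square tests and t-tests will be used to check whether the randomization has succeeded". The variables listed are personal information and functioning, NPI, caregiver burden, and the quality of life of both members of the dyad. The Clinical Dementia Rating (CDR), which is measured at T0 for inclusion, is not on the list. The rule then runs in two steps. Step one: "When significant differences are found at baseline, we will assess whether these attenuate the outcomes later in time". Step two: "If that is the case, we will control for these confounding variables in later analyses on the effects of the intervention".

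Under Effects, the primary model has no named covariate: "The condition (intervention vs. control) is the independent variable and the outcome measures across the three measurements are the repeated dependent variables". The T0 NPI score is therefore one of the repeated dependent measures. The four exploratory cluster models are handled differently. They fix a baseline term in advance, entering condition and "presence of clinically relevant symptoms within the respective clusters at baseline as independent variables".

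**The concern.** When allocation comes from a random list drawn up independently of the participants, and baseline is measured before allocation, any baseline difference between the arms is due to chance. A p-value below .05 then shows that an unlikely draw occurred, not that randomisation failed. A p-value above .05 does not show that a variable can safely be ignored.

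The protocol nevertheless makes a significant difference a necessary condition for adjustment. Two things follow. First, the value of a covariate lies mainly in how well it predicts the outcome, and the rule screens on something else, so a strong predictor that happens to be balanced has no way in. CDR, being unlisted, has no way in under any result. Second, the final decision rests on outcome data and has no criterion. The verb used for the second step could mean that the variable is associated with later NPI, or that adjusting for it changes the estimated treatment effect. On the second meaning, covariates would be chosen by their influence on the result. Two competent analysts could reach different primary models from the same data.

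**Working it through.** **Inputs from the protocol article.** Sample size calculation: "GPower: f = 0.15; alpha = .05; power = .80; repeated measures anova with 2 groups and 3 measurement points", correlation .50 between measurements, 30% drop-out, 53 per condition. **Assumptions, not in the document:** baseline tests at .05; their number (10 to 30) and independence; step two read as an association with the outcome at p < .05; a covariate–outcome correlation ρ of .3 to .7; a standardised effect of 0.5 for the power comparison.

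**1. The plan's own figure.** For the group-by-time interaction, λ = f²·N·m/(1−r) = 0.0225 × 74 × 3 / 0.5 = 9.99, with 2 and 144 degrees of freedom. Power is .806 at N = 74 and .795 at N = 72, so 74 reproduces. Then 74/0.70 = 105.7, rounded up to 106, or 53 per arm.

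**2. How often step one fires.** The chance of at least one significant baseline test among k is 1 − .95^k:
- k = 10: .40
- k = 20: .64
- k = 30: .79

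With 53 per arm, a continuous variable needs a gap of 1.983 × √(2/53) = 0.385 SD to be significant.

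**3. How often the model changes.** Take 15 covariates, 5 of them prognostic, and suppose that step two always passes a prognostic one. A prognostic covariate enters with probability .05, and an irrelevant one with .05 × .05 = .0025. The chance that at least one enters is 1 − .95⁵ × .9975¹⁰ = 1 − .774 × .975 = .25. This is an upper figure for that scenario, because step two will sometimes miss a real predictor.

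**4. What the rule leaves out.** In a simulation (20,000 runs per scenario, 53 per arm, one covariate, one continuous outcome), the prognostic covariate entered in 4.0% to 5.1% of trials, so it was left out in about 95%. Results at the .05 level:

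| ρ | Type I error: rule | Type I error: fixed in advance | Power: unadjusted | Power: rule | Power: fixed in advance |
|---|---|---|---|---|---|
| .3 | 4.6% | 4.9% | 72.6% | 72.5% | 76.1% |
| .5 | 4.1% | 4.7% | 73.1% | 74.0% | 84.1% |
| .7 | 3.7% | 5.1% | 72.7% | 74.7% | 94.5% |

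The rule performs almost like no adjustment and grows somewhat conservative as ρ rises. The unadjusted comparator is a follow-up-only test. The planned analysis already contains T0 NPI as a repeated measure, so the rows for ρ = .5 and .7 overstate what further covariates would add here. The ρ = .3 row, a gain of 76.1 − 72.5 = 3.6 percentage points, is arguably the more realistic guide for covariates other than baseline NPI.

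**The case against.** The best defence is that step two filters out noise, that the main model is otherwise fixed, and that no false positives result. Much of this stands. Effects fixes the outcome, the factor, the time points and the type of model; only the covariate set is open. An irrelevant variable gets in about 0.25% of the time. Simulated type I error is at or below about 5%, although that holds for the association reading of step two and was not examined for the change-in-effect reading.

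Three stronger inferences are tempting and are not supported.

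- *The primary result hangs on a coin flip.* The 40% to 79% counts trials with any significant baseline test. It ignores step two, after which adjustment occurs in about 25% of trials at most in the scenario above.
- *The rule costs a large share of precision.* In a simulation with 37 per arm, the standard error was 0.237 under the rule and 0.187 with adjustment fixed in advance for baseline and two covariates, a gap of 0.050. At r = .50 with one follow-up, a change score has standard error √(2/37) = 0.233 and a baseline-adjusted comparison √(1.5/37) = 0.201. About 0.031 of the gap, roughly 60%, therefore comes from how the primary model uses baseline, which would remain if the tests were deleted.
- *A significant NPI gap would distort the estimate.* Moving from change score to baseline adjustment shifts the estimate by (1−r) times the gap: 0.5 × 0.385 = 0.19 SD with 53 per arm, or 0.5 × 0.463 = 0.23 SD with 37. This needs NPI itself to be the significant variable, roughly a 5% event, and the shift largely corrects a chance imbalance. Nor does the protocol say how a variable that is already a dependent measure would be controlled for, so a switch of estimator is an inference.

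None of this rescues the rule. Step two can remove variables but cannot admit a balanced predictor. The rule is also stated outright, so it is not a detail left to an analysis plan.

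**Conclusion.** The concern holds in moderate form. The tests do not show whether randomisation succeeded. The covariate set of the primary model is settled only after outcomes are examined, by a check with no criterion, and prognostic variables without significant imbalance are left out about 95% of the time. The cost is a modest loss of precision and an analyst-dependent step in the primary analysis. A reader should not infer an inflated type I error or a primary analysis that is wholly unspecified.

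The 95% follows directly from testing at .05. The 40% to 79% and the 25% depend on the assumed number and independence of the tests and the assumed share of prognostic variables. NPI total, NPI distress and EDIZ are plausibly correlated, so the independence figures are approximate. The correction should be made, but the flaw is not fatal.

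**What to change.** Delete the significance tests and the conditional adjustment rule, and report baseline characteristics descriptively by arm. Name in advance a short covariate set from data already collected at T0, for example CDR category (0.5 or 1) and age, and use it whatever imbalance is observed. CDR and age are suggestions: the protocol does not say which variables predict NPI, so the investigators should choose and justify the set. Keep the baseline cluster status already fixed in the logistic models.

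If baseline NPI is to be a covariate, this is more than an edit to one paragraph. T0 is now one of the three dependent measures, so the primary model must be restated with T1 and T2 as outcomes and T0 as covariate. The sample size paragraph, written for three repeated measurements, would then need a matching sentence.

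The cost is a small rewrite of the analysis section and a few degrees of freedom. No new data are needed, and naming covariates in advance does not in itself change the target of 106.

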#### Missing values

Multiple imputation (five data sets) will be used to replace missing values and carry out the analyses on the pooled data set. Hence, all participants who were randomized can be included in the statistical analyses. The results from this imputed intention-to-treat sample will be compared to the results of the observed data only.

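### The missing-data rule describes one analysis of a pooled data set rather than pooled estimates from five analyses; followed literally, it understates standard errors

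*Protocol article*

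**What the plan says.** The Missing values section gives the rule in full: "Multiple imputation (five data sets) will be used to replace missing values and carry out the analyses on the pooled data set". It draws the consequence "Hence, all participants who were randomized can be included in the statistical analyses", and adds a check: "The results from this imputed intention-to-treat sample will be compared to the results of the observed data only". It does not say that the five data sets are analysed one by one, or that estimates and variances are combined across them.

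The Effects section applies a repeated-measures MANOVA to total NPI at T0, T1 and T2. Post-hoc simple contrasts compare T1 and T2 with T0.

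The Sample size calculation section gives the amount of missing data to expect: "Given the vulnerability of the participants and a high mortality rate, we expect a drop-out of 30"%. It ends with "Hence, 106 participants need to be included, 53 per condition".

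**The concern.** The instruction names the object to be analysed as a data set, not a set of results. There are two ways to turn five imputed data sets into one.

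- **Stacking.** The five copies are placed under one another. The software sees 530 rows where there are 106 participants.
- **Averaging.** Each missing value is replaced by the mean of its five imputations. The sample size is right, but the filled-in values vary too little and count as real observations.

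Both discard the between-imputation variance, which is the reason for imputing more than once. Standard errors come out too small and p-values too low. What is at stake is the imputed intention-to-treat result for the primary outcome, and any secondary outcome analysed the same way.

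**Working it through.** **Inputs from the Sample size calculation section.** "f = 0.15; alpha = .05; power = .80; repeated measures anova with 2 groups and 3 measurement points"; correlation .50 between measurements; 74 evaluable; 106 randomised, 53 per arm; 30% drop-out. From Missing values: five imputations.

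**Reproducing the plan's figures.** For the within-between interaction, lambda = f² × N × m / (1 − r) = 0.0225 × 74 × 3 / 0.5 = 9.99. With 2 and 2 × (74 − 2) = 144 degrees of freedom, power is 0.806. So "Hence, 74 participants are needed" is confirmed. Inflating for drop-out, 74 / 0.70 = 105.7, which rounds up to 106. The expected loss is 0.30 × 106 = 31.8, about 32 participants.

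**Size of the fault from stacking, without simulation.** Stacking multiplies the apparent sample by 5, so the standard error shrinks by about √5 even if nothing is missing: 1/√5 = 0.447.

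- For one contrast, the null is rejected when |Z| > 1.96 × 0.447 = 0.876, which has probability 0.38.
- For a 2-df test (large-sample), the 5% limit 5.99 becomes 5.99 / 5 = 1.198, and exp(−1.198 / 2) = 0.55.

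These are floors; missing data push the error rate higher.

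**Simulation under no effect.** Assumptions: 53 per arm, three normal measurements with all correlations .50, monotone random drop-out with half of it before T1, and proper normal-regression imputation with m = 5. Nominal level 5%, with 3,000 to 4,000 runs per cell.

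T2-T0 contrast at 30% drop-out:

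| Method | Mean SE / true SD of estimate | Type I error |
|---|---|---|
| Stacked | 0.39 | 45% |
| Averaged | 0.79 | 12% |
| Rubin's rules, m = 5 | 1.02 | 4.6% |
| Observed data only | 1.00 | 5.1% |

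The SE ratios explain the error rates. For stacking, 1.96 × 0.386 = 0.757 gives 0.45; for averaging, 1.96 × 0.785 = 1.54 gives 0.12.

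Group-by-time test, as planned for the primary outcome (two change scores tested jointly):

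| Method | 10% drop-out | 30% drop-out |
|---|---|---|
| Stacked | 59% | 64% |
| Averaged | 8% | 15% |
| Observed data only | about 5% | about 5% |
| Multi-parameter Rubin pooling, m = 5 | about 6% | about 5% |

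A repeat of the group-by-time runs at 30% gave 63% stacked and 15% averaged, which is the same within simulation error.

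**The case against.** The strongest reply is that *pooled* is the usual multiple-imputation word for results combined across data sets, so the phrase may be loose wording for a correct procedure. The article never says that data will be stacked or averaged. This stands as far as it goes: on that reading the error rate is right. It does not rescue the sentence as written, which attaches *pooled* to the data.

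The planned comparison with observed data also counts. A spuriously significant imputed result would sit beside a correctly sized one. The safeguard is partial, because the plan does not say which result governs if the two disagree.

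Three stronger readings may tempt a reader, and the document does not support them.

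- **That the primary p-value is undefined even with proper pooling.** It is not. The group-by-time test has two degrees of freedom, and multi-parameter pooling rules give it a defined p-value with about the nominal error rate. Which formula is used can be left to the analysis plan.
- **That five imputations are too few.** The error rate holds with five. For the planned T2-T0 contrast at an illustrative d = 0.5 (not the planning effect), power was 0.61 with 5 imputations and 0.66 with 40. That is a modest efficiency gain, not a correction.
- **That the plan imputes values for participants who have died.** The Missing values section does not mention death, its wording on including everyone is permissive, and a condensed article commonly leaves this to the full plan. The inference is reasonable, because the same article expects deaths among the drop-outs and states no exception, but it is an inference.

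**Conclusion.** The point holds as a fault in a stated rule, not as proof that the trial's standard errors will be wrong. If the sentence is followed literally at 30% drop-out, the type I error of the primary group-by-time test is about 64% with stacked data and 15% with averaged data. The valid alternative gives about 5%. If pooled results were meant, nothing in the analysis changes and only the wording needs repair.

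The percentages assume normal data and random drop-out. NPI totals are probably skewed, so the figures are illustrative. The direction does not depend on that assumption: either way of forming one data set ignores imputation uncertainty, and stacking inflates the error even with nothing missing.

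The handling of deaths is a secondary remark. The article does not say how many of the roughly 32 expected drop-outs would be deaths, so the effect on NPI or QALYs cannot be sized.

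**What to change.** Replace the sentence with one to this effect: missing values are multiply imputed; each imputed data set is analysed separately; the results are combined by Rubin's rules, with multi-parameter pooling for the group-by-time test and scalar pooling for the T1-T0 and T2-T0 contrasts. Raising the number of imputations above five is optional and costs only computing time.

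In the same place, limit the replacement of missing values to participants alive at the visit, so that NPI and EQ5D values after death are not filled in as if the person were living. This requires that dates of death are recorded.

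The design, sample size and assessments are unchanged. The cost is a change of wording and slightly more analysis work.
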